## Abstract

**Background:**

Research indicates that risky play benefits children’s risk assessment and risk management skills and offers several positive health effects such as resilience, social skills, physical activity, well-being, and involvement. There are also indications that the lack of risky play and autonomy increases the likelihood of anxiety. Despite its well-documented importance, and the willingness of children to engage in risky play, this type of play is increasingly restricted. Assessing long-term effects of risky play has been problematic because of ethical issues with conducting studies designed to allow or encourage children to take physical risks with the potential of injury.

**Objective:**

The Virtual Risk Management project aims to examine children’s development of risk management skills through risky play. To accomplish this, the project aims to use and validate newly developed and ethically appropriate data collection tools such as virtual reality, eye tracking, and motion capturing, and to provide insight into how children assess and handle risk situations and how children’s past risky play experiences are associated with their risk management.

**Methods:**

We will recruit 500 children aged 7-10 years and their parents from primary schools in Norway. Children’s risk management will be measured through data concerning their risk assessment, risk willingness, and risk handling when completing a number of tasks in 3 categories of virtual reality scenarios: street crossing, river crossing, and playing on playground equipment. The children will move around physically in a large space while conducting the tasks and wear 17 motion-capturing sensors that will measure their movements to analyze motor skills. We will also collect data on children’s perceived motor competence and their sensation-seeking personality. To obtain data on children’s risk experiences, parents will complete questionnaires on their parental style and risk tolerance, as well as information about the child’s practical risk experience.

**Results:**

Four schools have been recruited to participate in data collection. The recruitment of children and parents for this study started in December 2022, and as of April 2023, a total of 433 parents have consented for their children to participate.

**Conclusions:**

The Virtual Risk Management project will increase our understanding of how children’s characteristics, upbringing, and previous experiences influence their learning and ability to handle challenges. Through development and use of cutting-edge technology and previously developed measures to describe aspects of the children’s past experiences, this project addresses crucial topics related to children’s health and development. Such knowledge may guide pedagogical questions and the development of educational, injury prevention, and other health-related interventions, and reveal essential areas for focus in future studies. It may also impact how risk is addressed in crucial societal institutions such as the family, early childhood education, and schools.

**International Registered Report Identifier (IRRID):**

DERR1-10.2196/45857

## Introduction

### Background

How children learn to handle risk and avoid injuries is poorly understood by researchers. Injuries remain the leading cause of child death and a leading cause of hospitalization in high-income nations despite widespread prevention efforts. Among the leading mechanisms of injury are motor vehicle crashes (being a passenger in a car) [1] and falls (eg, from high playground equipment) [2]. Drowning, pedestrian, and cycling injuries also represent threats of serious injury and death [3]. Improved car safety has resulted in significant improvements in injury rates, but injury prevention efforts must be multifaceted, addressing the physical environment and individual risk factors [4]. One novel and promising approach to child injury prevention may be through improving children’s own ability to assess risk. In this regard, *play* appears to be an ideal context for children’s learning, as the pretend or nonliteral aspect allows the players to test out risky behavior, situations, or actions without the severe consequences of real life. *Risky play* has therefore emerged as a topic of interest for researchers, parents, teachers, policy makers, authorities, and others working with children over the last 20 years. A growing body of research investigates various aspects of risk-taking, including playful activities, and indicates that the concept reflects a basic aspect of human life.

The link between childhood risky play experiences and subsequent ability to cope with hazards of everyday life warrants investigation. A common definition of risky play is “thrilling and exciting forms of physical play that involve uncertainty and a risk of physical injury” [5]. Through observations and interviews with children and early childhood education and care (ECEC) staff, Kleppe et al [6] and Sandseter et al [7,8] identified eight categories of risky play: (1) play with great heights, (2) play with high speed, (3) play with dangerous tools, (4) play near dangerous elements, (5) rough-and-tumble play, (6) play where children go exploring alone, (7) play with impact, and (8) vicarious risk.

Qualitative studies suggest that children develop skills and learn to cope with risk through risky play that translates to real life and is retained for a lifetime [9-14]. Engagement in risk-taking activities leads to brain development, for example, and enhances the ability of 18- to 19-year-olds to predict outcomes, supporting the hypothesis that children and youth will learn risk assessment through risk experiences [15,16]. Moreover, there are indications that risky play in early childhood has a positive impact on the development of children’s own risk management skills [11,17]. Researchers also suggest that the ability to handle risk is a favorable evolutionary trait [18] and that outdoor risky play offers several positive health effects for children such as resilience, social skills, physical activity, well-being, and involvement [19,20]. In addition, there are indications that the lack of risky play and autonomy increases the likelihood of anxiety, both in childhood [21-24] and subsequently in adolescence and adulthood [18,25-29].

Children’s affective, cognitive, perceptual, and motor systems are all involved in children’s behavior and activities in an integrated manner. Children’s motor competence, including their capacity to execute fundamental motor skills as well as their perceived motor competence, therefore, impacts and is most likely reciprocally impacted by healthy risk-taking. Possessing high perceived or actual motor competence allows children to engage in different interactions with risky environments and tasks compared with children who possess lower perceived or actual motor competence because perception and action are intertwined processes occurring between the individual, the task, and the environment [30,31].

Despite its well-documented importance and the willingness of children to engage in risky play [5,6,32,33], there are indications that this type of play is increasingly restricted [34-37]. ECEC institutions restrict risky play because they fear being sued in case of child injury and they receive pressure from the insurance industry to avoid any injuries [32,35,36,38,39]. Moreover, parents restrict children from playing outdoors because they are concerned about traffic accidents [39-43], that children could be injured or kidnapped, or because they fear rainy or cold weather [39]. When children are prohibited from risky play through overprotection, there may be negative effects on their development.

The downward trend in children’s opportunities for risk-taking in play [44,45] may also have wider negative consequences. First, an increased focus on safety has resulted not only in greater restrictions on children’s movement but also less challenging and engaging play environments [35-37,46-50]. Second, there is concern that lack of play opportunities may result in negative long-term consequences such as reduced well-being and excessive or unhealthy risk-taking (eg, through risky substance use or sexual behavior).

As evidence accumulates concerning the benefits of risky play, both researchers and policy makers have begun to recognize the limitations of our current knowledge. Most existing data are based on descriptive studies and fail to offer rigorous data to address potential causal relationships between risky play and benefits to children’s health, development, and learning. The field hypothesizes that engagement in risky play in childhood may reduce the likelihood of subsequent anxiety, faulty decision-making, and excessive risk-taking later in life. However, those hypotheses are generally based on data from small samples and frequently lack the rigor of longitudinal designs, randomization, and control groups.

One reason for the sparsity of rigorous data is that the hypotheses are difficult to test empirically. There are obvious ethical issues with conducting studies designed to allow or encourage children to take physical risks with the potential of injury. There are also ethical barriers to restricting children from playing freely or to randomly assigning some children to play freely and others not. Thus, assessing the long-term effects of play choices is problematic. Creative methodologies such as Kretch and Adolph’s [51] and Adolph and Kretch’s [52] experiments with the visual cliff (ie, allowing children to cross narrow bridges without the real possibility of falling) or Morgan et al’s [53] laboratory-based activity room to assess behavior should be further developed, perhaps leveraging virtual reality (VR) technology [54,55] as a promising methodology. However, transferability of results from laboratory or other controlled environments to real-life contexts poses a potentially inappropriate leap [56]. There is a need to continue to develop VR, augmented reality, and other technologies to simulate real-life settings and strengthen ecological validity of research methods. Using VR or augmented reality enables researchers to test situations that would be too dangerous to investigate in real life. Adding measurements of bodily movement and eye-tracking equipment, mostly absent in the field, would contribute detailed data on children’s reactions to stimuli in their environments. Understanding connections between risk experiences and risk management is central to understanding how risky play affects overall health and development.

In the Virtual Risk Management—Exploring Effects of Childhood Risk Experiences through Innovative Methods (ViRMa) project, risk is defined as future uncertainties that can entail negative or positive outcomes [44]. Further, risk is seen as both objective and subjective [57,58]. *Objective *risk refers to an estimation of the probability of an adverse event and of the expected harm or loss. The ways in which objective factors are experienced as risky depend on the individuals and are referred to as *subjective risk*. Both personality and temperament traits as well as cognition [59-62] and previous experience [57,63] affect an individual’s subjective risk experiences and decisions. Risk decisions can be interpreted as representing a balance between an individual’s propensity to take risks, the potential rewards of risk-taking, the perceived *danger* in the situation, and *previous experience *with injuries or losses [57].

In the ViRMa project, we aim to explore risks that are relevant to children’s everyday life and that they can at least partly control themselves. These are risks where children’s dynamic choices and actions matter. To capture this and to develop scientific measures, we have developed a conceptual framework (in process to be published in a theoretical paper) to describe the dynamic process through which children manage risks, a framework that captures how the child acts in an environment with potential for risk and where their risk willingness (ie, the emotional drive to seek and take risk, overlapping conceptually with sensation seeking and risk seeking), risk assessments (ie, the cognitive process of evaluating risk throughout a risk situation), and risk handling (the behavioral or motor process of managing a risk) can be observed through their actions and behaviors. Overall, children’s dynamic risk management therefore represents the outcome of a defined task or the observable outcome of whether they fail or succeed in the risk situation.

### Study Objectives

The aim of the overall ViRMa project is to develop, test, and validate ethically appropriate, technologically innovative, and easy-to-use methods to explore the relationship between children’s risk experiences through play and daily activities and their risk management skills. We introduce methods that to our knowledge did not exist before ViRMa. Thus, the project focuses especially on method development and exploration concerning whether the methods are useful and valid to measure the relationships of interest.

This paper describes the protocol of the third stage in the ViRMa project. Stages 1 and 2 had the following aims: (1) develop VR, eye-tracking, and motion-capturing tools and software, plus psychometric scales and additional data collection methods to provide insight into how children assess and handle risk situations using ethical study designs; (2) conduct a small-scale pilot study to test the feasibility of the research methods, particularly the developed VR scenarios, the eye-tracking technology, and the motion capture system.

In the presently reported final stage, the tools and methods developed in stages 1 and 2 will be used for large-scale data collection. The aim of stage 3 is twofold: (1) establish measures for children’s risk management, suggestively split into risk willingness, risk assessment, and risk handling through the VR, eye-tracking, and motion-capturing data, as well as validating the questionnaires to a Norwegian context, and (2) explore how children’s past risk experiences through play and daily activities (collected through parent questionnaires) are associated with their risk management.

In this trial, we are measuring associations between behaviors in VR with demographics as a first step to validate the methods and explore relationships between children’s risk experiences, their motor skills, and their risk management skills. If we succeed with the stage 3 ViRMa project, the long-term goal for the project group is to further develop a large-scale project with children and parents from different countries and cultural contexts, preferably with longitudinal data collection. This would enable both comparative analysis across cultures and longitudinal data on how children’s motor skills and risk management skills develop over time in accordance with their opportunities for risk experiences.

## Methods

### Study Design

This study is a quantitative cross-sectional study of children’s risk management in VR scenarios, measuring their risk willingness, risk assessment skills, and risk handling skills as well as their motor skills. Cross-sectional data on children’s self-perceived motor skills and sensation seeking personality will also be collected. In addition, the study has a retrospective component that gathers extensive data from parents’ questionnaires concerning the children’s background experiences: parenting styles, parental risk tolerance, and children’s practical risk experience from childhood. Analyses will explore associations between cross-sectional data and retrospective data.

### Participants and Eligibility Criteria

We aim to recruit 500 children (50% girls and 50% boys) in second to fourth grade (7- to 10-year-old). This age group was chosen because we want to not only explore risk management skills among children as early in child development as possible but also consider practical matters such as the appropriate age to use current generations of VR goggles given their large size, weight, and functionality. VR technology develops rapidly, and studies involving even younger children would be an aim in the future. Further, children aged 7 to 10 years are likely familiar with navigating traffic and nature environments, while also remaining interested in exploring a playground, which reflects the tasks in the VR scenarios in this study. This is also an age group when children are more likely to behave independently and outside adult supervision, creating greater injury risk.

We aim to recruit children from both urban and rural primary schools in Norway because children in rural areas usually spend more time playing and being active in nature environments than children living in urban areas. The pilot study demonstrated that VR is a popular data collection method among children. To avoid excluding any children from a particular setting, we will select 4 primary schools from different parts of Norway and invite all children in the relevant age range at each school to participate. Inclusion criteria are as follows:

Between the ages of 7 and 10 years (grades 2, 3, and 4 in Norwegian schools)Informed consent obtained from parents to participateAssent obtained from the child to participate.

We will contact selected schools through the principal and ask if they are willing to participate. If they agree, parents will then be contacted through the school’s web-based information system, with information about the project and an electronic consent form provided. Children whose parents provide consent will then be placed on a participant list and names will be replaced with a random code. Children will also be asked for assent to participate, and if they decline, their name and code will be deleted.

Parents (both mothers and fathers) of children will be invited to complete the web-based survey.

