Global measures on the child’s risk assessment, risk willingness, risk handling, and management will be established using exploratory factor analysis [88] drawing on data from VR, eye tracking, and motion capturing from the VR street crossing, river crossing, and playground tasks. RMS error of approximation (RMSEA), standardized root-mean-square residuals (SRMR), comparative fit index (CFI), and Tucker-Lewis index (TLI) will be used to evaluate and refine the established measurement models. Acceptable model fit is defined as RMSEA <0.1, SRMR <0.1, CFI >0.9, and TLI >0.9 [89]. Chi-square and chi-square difference tests will be conducted between the fitted and saturated models. However, no absolute thresholds for chi-square are set, following the sensitivity to sample sizes and the possibility that this measure may yield less precise estimates of the parameters [88,90]. Factor loadings will be investigated with the use of *R*² estimates (item >0.25) and standardized factor loadings (item >0.40) [88]. To validate the psychometric scales in the Norwegian context, factor analysis will be used. The scales with predefined subscales (SSSYC, Perceived Movement Skill, and CPBQ) will be validated using confirmatory factor analysis, and the TRiPS will be evaluated using exploratory factor analysis [88]. Acceptable model fit is defined as RMSEA <0.1, SRMR <0.1, CFI >0.9, and TLI >0.9. Factor loadings will be investigated with the use of *R*² estimates (item >0.25) and standardized factor loadings (item >0.40) [88].

Because the participating children are nested within schools, generalized structural equation modeling and multilevel regression analysis will be used in the primary outcome analysis to explore how children’s past risk experiences through play and daily activities are associated with their risk management. Children’s past risk experiences through play and daily activities will be measured primarily through the CPBQ and TRiPS, whereas measures related to the child’s risk management will be obtained from global measures related to risk management from the VR simulation. The child’s age, sex, and other relevant background and demographic information, as well as their sensation-seeking personality (measured through the SSSYC), will be included in the models.

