## Results

Funding to conduct the ViRMa project was confirmed in June 2021. From August 2021 to February 2022, the project group developed the VR scenarios, including eye-tracking technology and motion capturing, translated the scales, and developed the questionnaires. We will conduct the data collection from January 2023 to May 2023.

Four schools were recruited as data collection sites, with a total of approximately 660 students in second to fourth grade (7-10 years old). We aim to enroll 500 children and their parents for participation. The recruitment of children and parents for this study started in December 2022, and as of April 2023, a total of 433 parents consented for their children to participate.

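### Siblings can enrol and the main exposures come from their shared parents, but the stated analysis allows for clustering by school only

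*Protocol article*

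**What the plan says.** Under Participants and Eligibility Criteria, four schools are selected and the team will "invite all children in the relevant age range at each school to participate". The inclusion criteria are age and grade, parental consent and child assent; none restricts enrolment to one child per family. On identification: "Children whose parents provide consent will then be placed on a participant list and names will be replaced with a random code". Under Data Collection Procedure, parents are emailed a survey link carrying a code that matches their child's, so that parent and child data can be paired.

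Under Analysis, past risk experience is measured mainly by the CPBQ and TRiPS, both completed by parents. The dependence between children is described in one place: "Because the participating children are nested within schools, generalized structural equation modeling and multilevel regression analysis will be used". Family is not mentioned as a level, and no family identifier is described. The same section sets P<.01 to limit type 1 error and plans factor analyses to validate the CPBQ and TRiPS in Norway.

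**The concern.** Inviting three adjacent grades in full makes it likely that some participants are brothers, sisters or twins. The CPBQ and TRiPS describe how a parent behaves and what a parent tolerates, so siblings' exposure scores should be strongly correlated. Siblings are also likely to resemble each other in how they manage risk. When exposure and outcome are both positively correlated within families, a model that treats siblings as independent understates the variance of the association. A school effect does not remove this, because it captures only differences between school averages.

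At stake is the error rate of the primary associations, which the article tried to protect with a stricter significance level. A smaller issue concerns the scale validation. If a parent of two participants completes the questionnaires once per child, one respondent enters the factor analyses as two.

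**Working it through.** **Figure to reproduce.** None. The article gives no derivation of the 500 and no allowance for dependence between children, so only the effect of the omission can be computed.

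**Inputs from the article**
- Target: "We aim to recruit 500 children".
- Pool: four schools "with a total of approximately 660 students in second to fourth grade" (Results).
- Consents by April 2023: 433, which is 433/660 = 65.6% of the pool. With take-up this high, siblings at the same school can be expected, but their number is not reported.
- Significance level .01. Sidedness is not stated; two-sided is assumed, so z = 2.576.

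**Inputs assumed, because the article gives none**
- s, the share of children with one enrolled sibling: 5-30%.
- ρx, the sibling correlation of the parent-reported exposure: 0.7-1.0.
- ρy, the sibling correlation of the outcome: 0.2-0.5. Strictly, this should be the correlation left after the model's covariates and school.

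**Formula.** Among n children, n·s belong to sibling pairs, giving n·s/2 pairs. Each pair adds 2·ρx·ρy to the variance of the slope's numerator, on a scale where n independent children contribute n. The total is n + n·s·ρx·ρy, so the factor by which the naive variance is too small is

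D = 1 + s·ρx·ρy.

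The correct standard error is √D times the reported one, the effective sample size is n/D, and the true two-sided error is 2·(1 − Φ(2.576/√D)).

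**Results**

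| Case | s | ρx | ρy | D | √D | Effective n of 500 | Effective n of 433 | True error at .01 |
|---|---|---|---|---|---|---|---|---|
| Low | 0.05 | 0.7 | 0.20 | 1.007 | 1.003 | 497 | 430 | 0.0103 |
| Middle | 0.20 | 1.0 | 0.35 | 1.070 | 1.034 | 467 | 405 | 0.0128 |
| High | 0.30 | 1.0 | 0.50 | 1.150 | 1.072 | 435 | 377 | 0.0163 |

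For the high case: D = 1 + 0.30 × 1.0 × 0.50 = 1.15; √1.15 = 1.072; 2.576/1.072 = 2.40, giving a two-sided error of about 0.016. Across the range the correct standard error is 0.3% to 7.2% larger than the reported one. If both correlations are positive, the error always runs in the anti-conservative direction.

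**The case against.** The strongest objection is that this is detail an article leaves to the full protocol or analysis plan. The article calls its analysis plan relatively general, gives school nesting as the reason for the chosen methods, and does not say that school is the only level. Generalized structural equation models and multilevel regression can both take a family level. This has some force: the identifier and the robust errors may be specified elsewhere. However, the article does state a dependence structure for the primary analysis, and that structure leaves out the level at which the exposure arises.

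A second objection is that the effect is small and rests entirely on assumptions. This stands. The relevant outcome correlation is the residual one, after age, sex, background, sensation seeking and school. If it were 0.1-0.3, with exposure correlation 0.7-0.9 and a sibling share of 10-30%, the true error would be about 0.0103-0.013. In an exploratory study, a shift of that size would seldom change a conclusion.

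A reader might also infer four stronger points that the article does not support:
- **The random code destroys the family link.** It does not. Deletion of name and code is stated only for children who decline assent, and survey links go to parents by email with the child's code. The link therefore exists for some time, and nothing says that it is destroyed for enrolled children.
- **Siblings have identical exposure scores.** The sample items quoted from both scales ask about one child, and the survey codes are child-specific. High correlation is plausible; identity is not stated.
- **A parent of two participants answers twice.** The article does not say whether such a parent answers once or once per child.
- **The unit of enrolment is confused because consents are counted in parents.** That line is a recruitment status report set beside the number of students and a target in children. It is a matter of wording, not an analysis denominator.

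**Conclusion.** The point holds as a limited one. Siblings are eligible, their main exposures come from shared parents, and the stated analysis accounts for schools but not families. Standard errors for the CPBQ and TRiPS associations would be slightly too small. Under the assumed ranges, the variance is understated by a factor of about 1.01 to 1.15 and the true error at the stated .01 level is about 0.010 to 0.016. The direction depends on positive sibling correlation in both exposure and outcome. The size depends on a sibling share that the article does not report. It is small to modest, and it can be corrected for as long as the participant list or the parent contact records allow families to be identified.

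**What to change.** - Add a family code to the participant list while names, child codes and parent emails are still linked. All siblings stay eligible.
- For the CPBQ and TRiPS associations, use family-clustered standard errors or a family random intercept, in addition to school.
- In the scale validation, cluster on the responding parent wherever one parent contributes more than one questionnaire. Use one questionnaire per parent as a sensitivity analysis only, because answers about different children may both be valid and discarding one would lose information.

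The cost is one extra column, one further model term and slightly larger standard errors. If few siblings turn out to be enrolled, the results will hardly change.
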